## Abstract

**Background:**

Lifestyle is one of the main determinants of people’s health. It is essential to find the most effective prevention strategies to be used to encourage behavioral changes in their patients. Many theories are available that explain change or adherence to specific health behaviors in subjects. In this sense the named Motivational Interviewing has increasingly gained relevance. Few well-validated instruments are available for measuring doctors’ communication skills, and more specifically the Motivational Interviewing.

**Methods/Design:**

The hypothesis of this study is that the Scale for Measuring Motivational Interviewing Skills (EVEM questionnaire) is a valid and reliable instrument for measuring the primary care professionals skills to get behavior change in patients. To test the hypothesis we have designed a prospective, observational, multi-center study to validate a measuring instrument. –Scope: Thirty-two primary care centers in Spain. -Sampling and Size: a) face and consensual validity: A group composed of 15 experts in Motivational Interviewing. b) Assessment of the psychometric properties of the scale; 50 physician- patient encounters will be videoed; a total of 162 interviews will be conducted with six standardized patients, and another 200 interviews will be conducted with 50 real patients (n=362). Four physicians will be specially trained to assess 30 interviews randomly selected to test the scale reproducibility. -Measurements for to test the hypothesis: a) Face validity: development of a draft questionnaire based on a theoretical model, by using Delphi-type methodology with experts. b) Scale psychometric properties: intraobservers will evaluate video recorded interviews: content-scalability validity (Exploratory Factor Analysis), internal consistency (Cronbach alpha), intra-/inter-observer reliability (Kappa index, intraclass correlation coefficient, Bland & Altman methodology), generalizability, construct validity and sensitivity to change (Pearson product–moment correlation coefficient).

**Discussion:**

The verification of the hypothesis that EVEM is a valid and reliable tool for assessing motivational interviewing would be a major breakthrough in the current theoretical and practical knowledge, as it could be used to assess if the providers put into practice a patient centered communication style and can be used both for training or researching purposes.

**Trials registration Dislip-EM study:**

NCT01282190 (ClinicalTrials.gov)

## Background

Lifestyle is one of the main determinants of people’s health. It is essential to find the most effective prevention and health-promotion strategies to be used by general practitioners to encourage behavioral changes in their patients.

Many theories are available that explain change or adherence to specific health behaviors in subjects. Many of these theories have resulted in actions that include brief advice and counseling of different intensity and frequency. In this sense, recently, the named “Motivational Interviewing” (MI) has increasingly gained relevance and, in some clinical situations, efficiency
[1]. MI was developed as a way to help people work their ambivalence and provoke change
[2]. It was a transtheoretical model derived from the Person-Centered Therapy, which combined an empathetic and understanding style of counseling
[3] with a straightforward method for resolving ambivalence in the direction of changing. Theoreticians have made this theory evolve by deepening their study of MI, which is currently defined as "a style of clinical skills for understanding patients’ motivations for behavior change in the interest of their health"
[4].

Finding solid evidence of MI effectiveness –which is currently being assessed by our research group-, is as important as having instruments available to assess to what extent clinicians use the motivational approach when interviewing their patients, and whether they use it properly or not. To detect the skills of the clinicians involved in clinical trials carried out for assessing the effectiveness of MI, is an important task. In this sense, the contributions published so far are very limited in number. There are two relevant instruments for assessing the abilities/techniques of the most orthodox and extended theoretical approach: that of Miller and Rollnick’s
[4], as concerns MI, the Motivational Interviewing Skill Code (MISC)
[5] and its abridged and enhanced version, the Motivational Interviewing Treatment Integrity (MITI)
[6]; and the Behavior Change Counseling Index (BECCI)
[7]. The former has only recently been proved to be reliable and effective in assessing MI skills and could be used both for clinical and research purposes
[8,9]. Scant studies have been published on the implementation of these instruments in Spain. There is only a research paper published by Spanish-speaking experts, although it has some methodological limitations that make it hardly adaptable
[10].

This is the reason why new instruments should be developed and tested, with the purpose of measuring general practitioners’ motivational skills when it comes to encourage behavior change in patients. Such instruments should be based on three aspects: 1) An eclectic approach including different strategies and skills suggested in different theories, which would allow researchers to assess the effectiveness of each of such instruments. This approach can be more useful for clinicians than other tools, which might be theoretically too rigid. 2) The instrument should be adapted to our social and cultural environment, and it should be proved effective in general practice, where these approaches, as well as their limitations and possibilities, are more frequently used and well known. For example, due to the primary care burden, professionals have difficulty in exceeding the usual average time per interview (which in Spain is about seven minutes).
[11] Therefore, it would be unrealistic to propose interventions of about one hour long, as those suggested by MITI. 3) Finally, in this context, any translation and adaptation of the existing tools would not represent a significant step forward and would involve a similar effort to that required for developing a new measurement scale.

In Spain, our research group has recently developed two scales (GATHA-Res, CICAA)
[12,13] for identifying clinical interviewing skills to improve clinical practice in trainers and researchers, which are based on a generic approach to primary care known as "patient-centredness"
[14]. The aim of this new approach is to focus on the ideas, beliefs and expectations that patients have regarding their condition, and on the possible action plans to be undertaken, while promoting patients’ involvement in decision-making. These scales have rendered good psychometric indexes, and have proved useful for the purposes intended. At the same time that they have also served as a basis for other more specific purposes, such as patient involvement in decision-making (CICAA-D)
[15].

For all these reasons, it would seem reasonable and relevant to use "patient-centered" clinical interaction as a starting point. This approach focuses on the relevance of building a “therapeutic empathy” with the patient -which meets MI principles. Similarly, it is also reasonable to found this new instrument on the same methodological principles as previous instruments, which were based on the assumption that clinical communication is a set of conducts that can be observed and measured as any other clinical skill
[16]. Therefore, such conducts should meet a number of requirements that are well-known in the context of primary care communication
[17]. Thus, a good measurement tool should be based on a well-defined model of professional-patient relationship, as well as include multiple observable categories (multidimensionality), and have appropriate and well-documented psychometric properties (validity and reliability), as well as practicability. Further, it is noteworthy that one of the most reliable assessment methods is used in this instrument: the evaluation of recorded interviews by external trained raters
[18].

With this project we try to test the hypothesis that a tool called "Assessment Scale motivational interviewing" (EVEM in Spanish) designed to assess whether the Spanish doctors have MI skills to promote in their patients behavioural changes have good psychometric properties, in terms of validity and reliability.

## Methods

The conceptual hypothesis has formulated so: “Is the Scale for Measuring Motivational Interviewing Skills (EVEM, acronym in Spanish of “Escala de Valoración de la Entrevista Motivacional”) a valid and reliable instrument to measure the skills of primary care professionals ?”.

The main objective of this study, therefore, is to validate the EVEM questionnaire for its use in clinical interviewing with patients suffering from dyslipidemia.

The specific objectives are:

1. Developing a scale and assess its qualitative validity;

1.a) Developing and identifying scale items -basing on the theoretical model- and preparing a draft questionnaire for assessing general practitioners’ motivational interviewing skills;

1.b) Conducting an assessment based on expert opinions: face, consensual and content validity;

2. Analyzing the psychometric properties and attributes of the scale:

2.a) Assessing the questionnaire’s validity and reliability:

2.a.1.-in terms of reproducibility and variability (inter-observer reliability, intra-observer agreement -test-retest);

2.a.2.-in terms of homogeneity (scale internal consistency);

2.b) Assessing the generalizability of EVEM reliability;

2.c) Assessing its dimensionality (factor analysis);

2.d) Refining the scale contents (response rate, item-total correlation, reliability).

2.e) Assessing the scale’s sensitivity to change.

### Study design

For testing our hypothesis we used two epidemiological designs: A qualitative study in its first stage (expert opinions, Delphi technique), and a quantitative, prospective, observational and multicenter study in its second stage. Figure
1 shows the study protocol design. This study approaches the complementary objective of the Dislip-EM project, a cluster randomized, controlled clinical trial designed to assess the effectiveness of Motivational Interviewing in reducing cardiovascular risk and improving lipid control in patients with hyperlipidemia
[19].

**Figure 1 F1:**
[figure not shown]
Scheme of the EVEM study design.

### Action plan

The procedure in each stage is as follows:

-Stage 1: design of a questionnaire (Objective 1.a). The scale is designed in consistency with the underlying theoretical model, with the analysis of the scientific literature available, and with scientific evidence on clinical communication
[3,5,6,20].

-Stage 2: qualitative validation (objective 1.b). To analyze the face and consensual validity of the questionnaire, a group of 15 key-informants specially trained in clinical communication was created. Then, Delphi-type methodologies were implemented in an iterative process of three e-mail rounds
[21]. Once this stage was completed, three versions were obtained from the first EVEM version (see Additional file
1). Further, a manual was prepared for the evaluator in two formats: an extended version and an abridged version.

-Stage 3: psychometric properties and attributes of the scale (Objective 2): Objective 2.a): intra-/inter-observer agreement/reliability:

2.a.1. Intraobserver reliability: four evaluators (two experts and another two non-experts in MI -previously trained in the use of EVEM- will assess twice, separately and independently the same sample of 18 interviews randomly selected –from the 162 interviews done with standardized patients- in a 4–6 week interval. Evaluators are general practitioners with clinical experience and advanced theoretical/practical knowledge on MI.

2.a.2. Interobserver reliability: for training purposes, expert raters will invite non-expert to watch motivational interviewing videos of different models (stages of change) and quality, for providing feedback to the EVEM scale. Both non-expert observers and the two experts will independently assess the 18 interviews to assess interobserver agreement.

2.b) Concomitantly, the reliability-generalizability coefficients will be estimated. Considering the results obtained by our research group in the validation process of a questionnaire for assessing patient-centered interviews, such coefficients are expected to be between six and nine interviews
[13].

## Statistical analysis

### Stage 2: qualitative analysis (objective 1.b)

In the third Delphi round, the relevance/value of the questionnaire items was weighted by using a five-degree ordinal score scale. From the results obtained, the arithmetic mean, mode, distribution intervals and variance of each item were estimated as a way to measure the level of agreement. Therefore, high variance would represent a low level of agreement on the relevance of each item, and vice versa.

### Stage 3: psychometric properties and attributes of the scale (objective 2)

To assess intra-/inter-observer agreement levels, the simple concordance index (SCI), the global concordance index and Cohen’s kappa index (κ) will be estimated
[22]. Absolute values will be provided, along with confidence intervals and p value (p < 0.05). Intraclass correlation coefficients will also be estimated
[22,23]. The results obtained will serve to assess the level of agreement for each task and dimension, and for the total score of the EVEM questionnaire.

Further, the Student’s-*t*-test will be performed to compare the pairs of means obtained from the total scale scores, and the Bland & Altman methodology will be implemented. The latter is a descriptive method for analyzing graphically the pattern of deviations from zero (total agreement) and for determining whether intraobserver differences decrease or not as the average score increases
[24]. To assess any potential relative bias (systemic difference between both observations), the means of the differences between the values obtained in each interview, their standard deviations (SD) and limits of agreement (mean of the differences ± 1.96 x SD) will be estimated.

To express reproducibility by the κ statistic, the classification suggested by Landis & Koch will be applied
[25]. Landis & Koch characterized κ <0.40 values as indicating slight agreement, 0.75-0.40 as good, and κ>0.75 as excellent agreement. For the interpretation of the intraclass correlation coefficient (ICC), the classification established by Jiménez will be used
[26], which characterizes ICC >0.90 as very good reproducibility; 0.71-0.90 as good; 0.51-0.70 as moderate; 0.31-0.50 as slight and <0.31 as poor or no reproducibility.

To assess the questionnaire’s homogeneity or internal agreement, Cronbach’s alpha coefficient (α) will be used. The extent to which the α coefficient changes when an item is removed will also be analyzed, to determine whether the questionnaire’s reliability is altered or not, and to evaluate whether a specific item should be discarded
[22,27].

The dimensionality of the EVEM scale will be analyzed by factor analysis, which will provide statistics on the underlying scale factors of the theoretical construct to be examined
[28]. Since there are no prior hypotheses on the specific components of the construct or on their potential correlation, an exploratory –rather than a confirmatory- analysis will be performed. The stages proposed by Norman & Streiner
[29] will be followed for factor analysis. The correlation coefficient between the different variables will be estimated by the Kaiser-Meyer-Olkin measure of sampling adequacy (KMO) and by Barlett’s test of sphericity.

The generalizability of the EVEM scale will be measured in each observer by the ICC, and the reliability of the scale total score will be assessed in a consecutive case series study, following Mercer et al. method
[30]. In competence measurement studies, for an evaluator to be considered reliable, it is agreed that they must obtain ICC values >0.856
[31].

Subsequently, the scale content will be refined. The response rate and item-total correlation will be estimated to test the discrimination capacity of the items. Finally, the item-total correlation will be computed by identifying the correlation between Pearson’s coefficient value for each individual item and the total score for the questionnaire, task and dimension or factor where the item was included, once the item has been discarded
[22]. It was determined that items with coefficients <0.30 would be discarded
[32].

The construct validity will be analyzed and the discrimination capacity of the scale will be determined by using the extreme-groups methodology
[33]. On such purpose, the two randomized groups created for the Dislip-EM project will be used: in one of the groups, clinicians will perform MI sessions (n=110), and in the other group, they will perform common clinical interviewing with their patients (no-MI group) (n=110). The correlation between the scale and other variables will also be assessed. Finally, the correlation between the scores obtained with the EVEM scale and the endpoints obtained with the “parent” study (Dislip-EM project) will be analyzed.

Sensitivity to change will be assessed by two methods:

a) By measuring the impact of special training: the hypothesis will test whether the GPs in the Intervention Group (IG) improve their MI skills after joining the training program. Significant statistical differences are expected to be found between the mean scores obtained on the EVEM scale by the Intervention Group and those obtained by the professionals in the Control Group (CG).

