### Sample size

The sampling unit is the video recording of a clinical interview. From a general approach, most of authors agree that, in questionnaire validation studies, a sample size of 200–300 or 5–10 participants (in this case, clinical interviews) per scale variable would be adequate
[22,27,29]. Thus, considering that the last version of the scale has 16 items, the number of interviews required would be 80–160.

To calculate the sample size required to estimate inter-/intra-observer agreement, the formula developed by Norman & Streiner
[30] was used. They establish that the desirable minimum sample size can be estimated by the formula n= 2 x C^2^, where C is the number of answer categories. As the scale has three answer categories, the desirable minimum sample size is 18 interviews.

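### KMO and Bartlett's test are named as estimators of the inter-item correlation, which they are not; and kappa is named without weights for three-category answers that the plan otherwise treats as ordered

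*Protocol article*

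**What the plan says.** All of this is in the Protocol article.

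- **Agreement statistics** (Statistical analysis, Stage 3): "the simple concordance index (SCI), the global concordance index and Cohen’s kappa index (κ) will be estimated". The next lines add that "Intraclass correlation coefficients will also be estimated", and that the results serve to "assess the level of agreement for each task and dimension, and for the total score of the EVEM questionnaire". Bland and Altman limits and paired t-tests on the total score are also planned. No weighting for kappa is stated.
- **Grading of kappa** (same section): "κ <0.40 values as indicating slight agreement, 0.75-0.40 as good, and κ>0.75 as excellent agreement". The ICC has its own five-band scale.
- **Answer categories** (Sample size): the rule for the reliability sample is twice C squared, with C counting the response options. Applied to this scale, it reads: "As the scale has three answer categories, the desirable minimum sample size is 18 interviews".
- **Factor analysis** (Statistical analysis, Stage 3): an exploratory analysis following cited textbook stages. "The correlation coefficient between the different variables will be estimated by the Kaiser-Meyer-Olkin measure of sampling adequacy (KMO) and by Barlett’s test of sphericity". The type of correlation matrix to be factored is not named.
- **Item-total correlations** (same section): Pearson, with items below 0.30 discarded.

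**The concern.** There are two separate points.

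**Factor step.** The sentence on KMO and Bartlett's test assigns them a task that neither can do. It is also the only sentence saying where the correlations for the dimensionality objective (2.c) come from. As written, the input to the factor analysis is misdescribed and the matrix is left unnamed.

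**Rater agreement.** Cohen's kappa without qualification is normally read as unweighted. The sample-size rule takes C as the number of answer categories, which ties the agreement analysis to the three-category answers. Elsewhere the plan treats these answers as scores with an order. Unweighted kappa then counts a disagreement between neighbouring categories the same as one between the two ends. For a rating scale these are very different findings about the raters, yet one pair of cut-offs is applied. An item can land in a different band from the one that a distance-sensitive measure would give it, and the plan does not say which grade governs when kappa and the ICC disagree.

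**Working it through.** **Plan's own figures.** With C = 3, n = 2 x 3^2 = 18. With 16 items, 5 x 16 = 80 and 10 x 16 = 160, which matches "considering that the last version of the scale has 16 items, the number of interviews required would be 80–160". Both reproduce.

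**What KMO and Bartlett's test do.** Let R be the correlation matrix of the 16 items. It holds 16 x 15 / 2 = 120 distinct correlations.

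- KMO = sum of r² / (sum of r² + sum of squared partial correlations), over all item pairs. The partial correlations come from the inverse of R.
- Bartlett's statistic is a multiple of -ln|R| and tests whether R is an identity matrix, on 120 degrees of freedom.

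Both take R as input. One returns an index and the other a test statistic. Neither returns any of the 120 correlations.

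**Kappa on assumed tables.** The article gives no agreement tables, so these are illustrations with 18 interviews and two ratings each. Kappa = 1 - (observed weighted disagreement) / (chance-expected weighted disagreement). Unweighted: every disagreement counts 1. Quadratic: one step counts 0.25, two steps count 1.

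Table A, four adjacent disagreements: [[5,1,0],[1,4,1],[0,1,5]], all margins 6.
- Unweighted: observed 4/18 = 0.222; expected 1 - 1/3 = 0.667; kappa = 0.667.
- Quadratic: observed 4 x 0.25/18 = 0.0556; expected (4 x 0.25 + 2 x 1)/9 = 0.333; kappa = 0.833.

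Table B, four extreme disagreements: [[5,0,2],[0,4,0],[2,0,5]], margins 7, 4, 7.
- Unweighted: observed 4/18 = 0.222; expected 1 - (49 + 16 + 49)/324 = 0.648; kappa = 0.657.
- Quadratic: observed 4/18 = 0.222; expected (0.25 x 112 + 98)/324 = 0.389; kappa = 0.429.

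Other assumed 18-interview tables, with the plan's band in brackets and the two-way absolute-agreement ICC:

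| Pattern | Unweighted | Quadratic | ICC |
|---|---|---|---|
| 4 adjacent (Table A) | 0.67 (good) | 0.83 (excellent) | 0.84 |
| 6 adjacent | 0.50 (good) | 0.73 (good) | 0.74 |
| 8 adjacent | 0.33 (slight) | 0.67 (good) | 0.68 |
| 4 two-step, margins 6, 6, 6 | 0.67 (good) | 0.33 (slight) | 0.35 |
| 6 mixed | 0.50 (good) | 0.50 (good) | 0.51 |

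The band moves up, down or not at all. In every row the ICC is within about 0.015 of quadratic kappa. On the plan's own scales the eight-adjacent row reads slight by plain kappa and moderate by ICC; the four-two-step row reads good by plain kappa and slight by ICC.

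**Pearson on three-category items.** Simulated from an assumed bivariate normal cut into three categories, evenly or with the same skew on both items, underlying correlations of 0.30, 0.50 and 0.70 become 0.21–0.24, 0.37–0.41 and 0.55–0.59. With an underlying 0.40, the result is 0.32 for an even split, 0.28 for a 70/20/10 split on both items, and 0.22 for opposite skews. The loss varies with item difficulty.

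**The case against.** The strongest reply is that little here is settled by the article. It never calls kappa unweighted, and the weighting scheme is a detail that a condensed article may leave to a fuller document. It does not call the three categories ordered, and the item form is not shown. It reports agreement per task, dimension and total, so item-level kappa is inferred from the sample-size rule. It also plans the ICC, which credits near-misses almost exactly as quadratic kappa does. Even the extreme-disagreement Table B stays in the good band after weighting (0.66 to 0.43). On the factor step, a misworded sentence does not remove the matrix from which KMO and Bartlett's test must be computed.

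Most of this stands, and it limits the point. A reader might infer that agreement will be misgraded; the article does not support that, because the direction depends on unseen ratings and a distance-sensitive measure is already planned. A reader might also infer that the factor analysis has no suitable correlation matrix; that is unsupported too. The matrix type is simply unstated, Pearson is named for item-total correlations and not for the factor matrix, and attenuation makes correlations smaller without making them unusable. Requiring a polychoric analysis, or dropping Bartlett's test, would be a trade-off rather than a correction: polychoric estimates can be unstable when a category is nearly empty.

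Two things survive. The KMO and Bartlett sentence is not an omission; it states an estimator, and the statement is wrong. And the ICC does not remove the fixed bands attached to plain kappa, which can conflict with the ICC grade with no rule for which prevails.

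**Conclusion.** The point holds in limited form. The sentence on KMO and Bartlett's test is an error on the face of the text and should be corrected, with the factored matrix named. The kappa part is a recommendation for a better method. It rests on two assumptions: that the three categories are ordered, which the total score, ICC and Pearson item-total correlations imply; and that kappa without qualification means unweighted. On those assumptions plain kappa hardly distinguishes four near-misses from four reversals in 18 interviews (0.67 against 0.66), while quadratic kappa does (0.83 against 0.43). The tables are invented, so they show what can happen, not what will. The overall consequence is modest because the ICC is already planned.

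**What to change.** 1. Reword the factor-analysis sentence: KMO and Bartlett's test will be used to check whether the inter-item correlation matrix is suitable for factoring. Name the matrix that is factored. Because items have three categories, a polychoric matrix can be added as an optional sensitivity analysis; sparse categories may then need collapsing.
2. State that the answer categories are ordered, if they are. Report weighted kappa with a confidence interval, state the weights, and apply the 0.40 and 0.75 bands to that statistic. Keep simple agreement and the planned ICC alongside.

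The cost is analysis-plan wording and standard software, with no additional interviews or ratings. The downside is minor: the choice of weights has to be stated in advance, and quadratic-weighted kappa will largely agree with the ICC already planned.
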